### Outcomes

Assessment of efficacy will be carried out by evaluation of imaging examination at each follow-up. If applicable, response to treatment will be evaluated according to the RECIST criteria (version 1.1) and classified as complete response (CR), partial response (PR), stable disease (SD) and progressive disease (PD). 

The primary outcome is estimated as the difference between the intervention and the control group in local control rate in 1 year. Local control rate is judged to have been attained if there is no evidence of PD at the primary site based on imaging findings and clinical examination at follow-up. However, distant metastasis and second primary cancer are not belonged to PD at the primary site in accordance with RECIST criteria (version 1.1) [28].

Secondary outcomes are a) progression-free survival (PFS), defined as the time from randomization to the earliest occurrence of PD in whole body or death due to any cause; PD in whole body includes PD at the primary site, distant metastasis and second primary cancer; b) overall survival (OS), from the date of randomization to the date of death from any cause or last date when the participant is alive; c) QOL evaluated using the European Organization for Research and Treatment of Cancer QOL Questionnaire (EORTC QLQ-C30 and QLQ-H&N35) of Chinese version; and d) safety of treatment.

### Sample size estimation

Based on medical record of subjects with inoperable salivary gland malignancies in Peking University Cancer Hospital & Institute and in Peking University School and Hospital of Stomatology, local control rate in 1 year was 81 % among subjects with I-125 PBT, and 45 % among subjects with IMRT. Based on a difference of 36 % between groups on the primary outcome, a total of 72 participants are required to provide 90 % power, with the use of two-sided significance level of 0.05. Assuming a 20 % drop-out rate, approximately 90 subjects (or 45 subjects per arm) will be enrolled.

### Statistical analysis

Analyses will be made using SAS statistical software (version 9.3, SAS Institute, Cary, NC, USA) by researchers at the Peking University Clinical Research Institute. The primary analyses will be done on an intent-to-treat basis and the last observation carry forward (LOCF) is used for missing values. Descriptive statistics will be used to summarize demographic and clinical characteristics of subjects randomised to the intervention and control group. The difference between two groups on demographic and clinical characteristics, response rate and drop-out rate will be compared using t-tests (or Wilcoxon rank sum test) and chi-square test/Fisher’s exact test as appropriate.

Primary outcome (local control rate in 1 year) analyses will be carried out using chi-squared tests. The survival curves (PFS and OS) are estimated by the Kaplan-Meier method, and log-rank test is used to test the null hypothesis that the respective curves are equal between the two groups. A two-sided significance level of 5 % is used. A covariance model will be used to compare the QOL between two groups by adjusting the difference of baseline. The incidence of adverse events between two groups is compared with the chi-square test/Fisher’s exact test.

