### Inclusion criteria

In the study, inclusion criteria are as follows: (1) willing to participate and sign informed consent; (2) aged 18–80 years; (3) malignancies originating from major or minor salivary glands based on pathological and/or cytological diagnosis, including primary or recurrent tumors; (4) with inoperable tumors, including unresectable primary locally advanced tumors; unresectable recurrent tumors; and unable to undergo surgery due to other medical comorbidities or refusal of surgery out of personal preference, and being T3/T4 T-stage; (5) with at least one measurable tumor focus based on RECIST criteria and imaging diagnosis completed in 30 days before enrollment; (6) expected survival time ≥3 months; (7) Karnofsky performance status ≥60; (8) adequate hematopoietic function of bone marrow in previous 7 days: hemoglobin ≥9 g/dL, white blood cell count ≥3.0 × 10^9^/L, neutrophils count ≥1.5 × 10^9^/L, platelet count ≥100 × 10^9^/L; (9) normal liver and kidney function in previous 14 days: total bilirubin in serum ≤1.5 times the upper limit of normal (ULN), alanine transaminase and aspartate transaminase ≤3 times ULN, creatinine ≤1.5 times ULN; (10) willing to take measures to prevent pregnancy.

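### LOCF on the binary primary endpoint scores patients who drop out or stop for a second cancer before month 12 without local progression as 1-year local controls, so each arm's rate is biased upward

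*Protocol article*

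**What the plan says.** The Statistical analysis section sets one rule for incomplete data. In the primary analyses, which are by intent to treat, the "last observation carry forward (LOCF) is used for missing values". The primary outcome is then compared by a chi-squared test.

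The Outcomes section defines the endpoint: "The primary outcome is estimated as the difference between the intervention and the control group in local control rate in 1 year". Success is defined by the absence of an event: "Local control rate is judged to have been attained if there is no evidence of PD at the primary site". The same section adds that "distant metastasis and second primary cancer are not belonged to PD at the primary site".

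The section on initial screening, assessment and follow-up schedules visits at 2, 4, 6, 9 and 12 months and on to 24 months. It ends a patient's follow-up once recurrence, another malignancy or death is confirmed.

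The Sample size estimation section expects incomplete follow-up: "Assuming a 20 % drop-out rate, approximately 90 subjects (or 45 subjects per arm) will be enrolled".

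**The concern.** Read together, these rules turn an early status into a 1-year result. A patient last seen without local progression at month 2, 4, 6 or 9 who then drops out has no 12-month assessment. Under LOCF the earlier status stands in for it, and the patient is counted as controlled at 1 year. A patient who stops follow-up because of a second cancer before month 12 is treated in the same way, and here the gap arises from the protocol's own follow-up rule.

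LOCF has no compensating error for this endpoint. A patient who has progressed locally stays progressed, while a patient who has not may still progress before month 12. The carried value is therefore right or too favourable, never too unfavourable.

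At stake is the headline result of the trial: the two reported rates, their difference and, if loss differs between arms, the 5% significance level. The treatments are open-label and very different in form (a seed implant versus 33 fractions over 6 to 7 weeks), so unequal loss is possible, although the documents do not predict it.

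**Working it through.** **Inputs from the protocol article.** Planned 1-year local control is 0.81 (I-125 PBT) and 0.45 (IMRT). Two-sided alpha is 0.05, power 90%, 72 evaluable patients, 20% drop-out, 45 enrolled per arm.

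**Assumptions, not in the documents.** The hazard of local progression is constant over the year, leaving is unrelated to local progression, and the timing of loss and its split between arms are as stated in each case.

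**Step 1: the plan's own figure.** The two-proportion formula with pooled variance and no continuity correction, with mean rate 0.63, gives

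n = [1.960·√(2·0.63·0.37) + 1.282·√(0.81·0.19 + 0.45·0.55)]² / 0.36² = 35.7, so 36 per arm, 72 in total.

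72 / 0.80 = 90. Both stated figures reproduce.

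**Step 2: the rate that LOCF reports.** With 1-year control p, status at time t (in years) is p^t. If leaving times are spread evenly over the year, the mean carried-forward rate is (1 − p) / (−ln p):

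- PBT: 0.19 / 0.211 = 0.902
- IMRT: 0.55 / 0.799 = 0.689

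With a share q lost before month 12, LOCF rate = (1 − q)·p + q·mean.

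**Step 3: equal loss, q = 0.20 in each arm.**

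- PBT: 0.8·0.81 + 0.2·0.902 = 0.828
- IMRT: 0.8·0.45 + 0.2·0.689 = 0.498
- Difference: 33.1 points (from unrounded rates) instead of 36
- Exact power of the chi-squared test at 45 per arm: about 93%

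Using the planned visit times instead (last status at month 2, 4, 6 or 9, averaged) gives 0.831 and 0.503, a difference of 32.7 points. It ranges from 30.6 if the last visit is at month 2 to 34.9 if at month 9.

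With no true difference and equal loss, LOCF creates no spurious difference. At 60% true control the exact type I error is about 5.2%, which reflects the discreteness of the test.

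**Step 4: unequal loss when the planned effect is real** (loss spread over the visits, normal-approximation check).

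| Loss, PBT / IMRT | PBT | IMRT | Difference |
|---|---|---|---|
| 30% / 10% | 0.841 | 0.477 | 36.4 points |
| 10% / 30% | 0.820 | 0.530 | 29.1 points |

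So the difference can end up slightly above or well below the true 36 points.

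**Step 5: unequal loss with no true difference** (60% control in both arms, loss of 10% and 30%). The mean carried-forward rate is 0.40 / 0.511 = 0.783.

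- Spread over the year: 0.9·0.60 + 0.1·0.783 = 0.618 and 0.7·0.60 + 0.3·0.783 = 0.655. The spurious difference is 3.7 points, exact type I error 6.7%.
- All loss before the first visit, every lost patient scored as controlled: 0.9·0.60 + 0.1 = 0.640 and 0.7·0.60 + 0.3 = 0.720. The spurious difference is 8.0 points, type I error 13.4%. This is an extreme bound.

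**The case against.** The strongest reply is that the harm is modest at the only drop-out figure the protocol gives. That stands. Equal 20% loss spread over the year costs 2.9 points, shrinks the effect rather than inflating it, and leaves power above the planned 90%. The larger error rates need an imbalance between arms, and the largest also needs all loss to precede the 2-month visit. Nothing in the documents supports either. The plan also compares drop-out rates between arms, which would reveal an imbalance but would not correct for it.

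Four stronger readings are tempting and are not supported:

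- **LOCF wrongly turns early deaths into successes.** A reader might infer this, especially as eligibility requires only "expected survival time ≥3 months". But leaving death out of local failure follows from the endpoint definition. Death is captured in overall survival and in PFS, which is "the time from randomization to the earliest occurrence of PD in whole body or death due to any cause". If 10% of patients die at times spread over the year, regardless of local status, LOCF gives 0.9·0.81 + 0.1·0.902 = 81.9% and 0.9·0.45 + 0.1·0.689 = 47.4%. One minus the cumulative incidence of local progression, with death as a competing event, gives the same two figures. The survival criterion is also only an eligibility floor.
- **Every early leaver is scored as controlled.** Response is assessed at follow-up, so a patient with no visit after baseline has no response to carry. The article does not say how that patient is scored.
- **About 18 of 90 patients are affected.** This is 20% of 90 and an upper bound. Follow-up runs to 24 months, and a patient lost after month 12 has a 12-month status.
- **The sample size contradicts the analysis.** Enlarging the sample for drop-out while analysing everyone randomised is not a contradiction.

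It might also be said that a condensed article leaves missing-data detail to the full protocol or SAP. That would answer a complaint that sensitivity analyses are absent, but not this one: the article states a rule, and the stated rule gives a wrong rate.

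**Conclusion.** The point holds for patients who drop out, or stop follow-up for a second cancer, before month 12 without local progression. For them LOCF reports an earlier status as a 1-year result, and each arm's rate can only be biased upward. The direction of bias in the difference is not fixed.

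With 20% loss per arm before month 12, the bias is 1.8 points for PBT (82.8 − 81), 4.8 for IMRT (49.8 − 45) and 2.9 in the difference, towards no effect. Power and type I error are not materially harmed in that case. Under an assumed 10% versus 30% imbalance with no true difference, the error rate rises moderately, to 6.7%; 13.4% is a bound, not an expectation.

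These sizes rest on constant hazards, loss unrelated to local progression, and assumed timing and split of loss. If patients leave because they are deteriorating locally, the upward bias in each rate would be larger.

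This should be fixed, because it affects the primary endpoint and the remedy is cheap. It does not by itself invalidate the trial.

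**What to change.** Remove LOCF for the primary outcome and replace it with the following:

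- **Main analysis.** Time from randomisation to progression at the primary site, as assessed by the independent board, in all randomised patients. Censor patients who drop out or stop follow-up for a second cancer at their last primary-site assessment. Treat death without local progression as a competing event. Report 12-month local control as one minus the cumulative incidence, and compare the arms as a difference with a 95% confidence interval and a test.
- **Sensitivity analysis.** Count every patient without a 12-month assessment as a failure, unless local progression status at 12 months is otherwise known. With 20% missing in each arm and missingness unrelated to outcome, this gives 0.8·0.81 = 64.8% and 0.8·0.45 = 36.0%, a difference of 28.8 points with power of about 79% (normal approximation, 45 per arm). It is a deliberately harsh check, not a candidate for the main analysis.
- **Supplementary estimand, if wanted.** Alive and locally controlled at 12 months. This answers a different question and should not be presented as a correction of LOCF.

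The cost is wording in the protocol and SAP; the planned visits already supply the data. The downsides are a slightly wider interval than a filled-in two-by-two table gives, a less simple headline statistic, and reliance on censoring being unrelated to local progression, which the sensitivity analysis probes.

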## Methods and design

### Trial design and setting

The study is conducted as a single center, prospective, randomised controlled trial with balanced randomisation (1:1) for subjects who have inoperable malignant salivary gland tumors are randomised to receive either I-125 PBT or IMRT. Subjects are stratified by tumor size (≤4 cm vs. >4 cm) and neck lymph node metastasis (yes vs. no). Subjects are recruited continuously by oncologists at Department of Oral and Maxillofacial Surgery, Peking University School and Hospital of Stomatology which is the only department to treating salivary gland malignancies by I-125 PBT in China.

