### Randomization

Central randomization based on interactive web response system (IWRS,Brightech Clinical Information Management System) is carried out by Peking University Clinical Research Institute, which is independent of the trial administration office. The allocation sequence is computer-generated 1:1 with dynamic randomization system and is stratified by tumor size and neck lymph node metastasis.

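### Allocation is balanced on tumour size and neck nodes, but the planned chi-squared and log-rank tests use neither factor: valid, but mildly conservative and inefficient if the factors are prognostic

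*Protocol article*

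**What the plan says.** The Randomization section of the protocol article states: "The allocation sequence is computer-generated 1:1 with dynamic randomization system and is stratified by tumor size and neck lymph node metastasis". Trial design and setting gives the cut-offs, 4 cm for size and presence or absence of neck node metastasis, so there are 2 × 2 = 4 strata.

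The Statistical analysis section fixes the tests. For the primary outcome: "Primary outcome (local control rate in 1 year) analyses will be carried out using chi-squared tests". For PFS and OS: "log-rank test is used to test the null hypothesis that the respective curves are equal between the two groups". The abstract names the same tests. None is described as stratified or adjusted. The one adjustment named is for quality of life: "A covariance model will be used to compare the QOL between two groups by adjusting the difference of baseline".

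Sample size estimation assumes that "local control rate in 1 year was 81 % among subjects with I-125 PBT, and 45 % among subjects with IMRT" and concludes that "a total of 72 participants are required to provide 90 % power", raised to 90 for 20% drop-out.

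**The concern.** Balancing allocation on a prognostic factor removes most of that factor's contribution to chance differences between the arms. A plain chi-squared or log-rank test still counts that contribution in its variance, as if allocation had been simple randomisation. Its standard error is then too large, the test rejects less often than 5% under the null, and some power is given up.

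At stake is efficiency in a small trial of a rare disease. The planned 36-point difference comes from medical records at two hospitals. The Discussion calls existing evidence sparse and observational, so a smaller true difference is plausible, and efficiency counts for more there. No hazard ratio or power is stated for PFS or OS.

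**Working it through.** **1. The plan's own figure.** Inputs from Sample size estimation: p1 = 0.81, p0 = 0.45, mean 0.63, two-sided α = 0.05, power 90%.

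n per arm = [1.960·√(2 × 0.63 × 0.37) + 1.282·√(0.81 × 0.19 + 0.45 × 0.55)]² / 0.36² = (1.338 + 0.812)² / 0.1296 ≈ 35.7, so 36 per arm and 72 in total; 72/0.80 = 90.

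This reproduces exactly and is the formula for the plain chi-squared test. Power is 90.3% at 36 per arm and 95.5% at 45 per arm.

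**2. The two tests.**
- Plain: (p̂1 − p̂0)² / [p̂(1 − p̂)(1/n1 + 1/n0)].
- CMH: [Σ(xk − n1k·mk/nk)]² / Σ[n1k·n0k·mk(nk − mk) / (nk²(nk − 1))]. In stratum k, xk is the number controlled on I-125, mk the number controlled in both arms, n1k and n0k the arm sizes, and nk their sum.

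**3. Why the plain test is conservative.** The overall variance splits as p(1 − p) = Σwk·pk(1 − pk) + Σwk(pk − p)². Balanced allocation largely removes the second term from the treatment contrast, but the plain test keeps it.

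Example, all assumed: factor prevalences 50% and 40%, odds ratio 3 per factor, common rate 45%. The shares with no, one or both adverse factors are 0.30, 0.50 and 0.20, with control rates 0.68, 0.42 and 0.19.
- Within-stratum variance: 0.30 × 0.68 × 0.32 + 0.50 × 0.42 × 0.58 + 0.20 × 0.19 × 0.81 = 0.218.
- Variance used by the plain test: 0.45 × 0.55 = 0.2475. The ratio is 0.88.
- Approximate size: 2[1 − Φ(1.96/√0.88)] = 2[1 − Φ(2.09)] ≈ 3.7%.

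Simulation of this setting with 72 patients gives 3.4% under minimisation and 3.5% under permuted blocks, so the choice of balancing scheme hardly matters.

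**4. Simulation with 90 patients** (assumed 60% >4 cm and 30% node-positive, balance within strata). The protocol gives no prognostic strength, so it is ranged from none upwards.

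| Odds ratio per factor | Size, chi-squared | Power at 72% vs 45%, chi-squared / CMH |
|---|---|---|
| 1 | about 5.0% | no material difference |
| 1.5 | 4.7% | 74.0 / 74.7% |
| 2 | 4.1–4.3% | 73.9 / 75.6% |
| 3 | 3.6–3.8% | 75.1 / 79.0% |
| 4 | 3.0–3.3% | 76.4 / 81.9% |

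CMH size stays at 4.9–5.2%. The largest gain is 81.9 − 76.4 = 5.5 points. At the planned 81% vs 45% the gain is 0.3 to 1.2 points for odds ratios 2 to 4.

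**5. Simulation with 72 patients** (assumed prevalences 50% and 40%, minimisation, 40,000 runs per setting).

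| Odds ratio per factor | Power at 81% vs 45%, chi-squared / CMH | Power at 70% vs 45%, chi-squared / CMH |
|---|---|---|
| 1 | 90.5 / 89.8% | 57.3 / 57.1% |
| 2 | 91.1 / 91.2% | 57.2 / 59.0% |
| 3 | 91.7 / 92.8% | 57.5 / 62.3% |
| 5 | 92.5 / 95.0% | 57.4 / 66.6% |

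If the factors are not prognostic, CMH costs 90.5 − 89.8 = 0.7 points. The last row is an extreme beyond the 1-to-4 range.

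**6. Log-rank, illustrative only** (90 patients, 24 months of follow-up, assumed treatment hazard ratio 0.5 and control median 15 months in mid-risk strata, 3,000 runs). For stratum hazard ratios of 1, 1.5, 2 and 3 per factor, plain size is 5.2, 4.4, 3.4 and 2.5%; the stratified test holds 5.0–5.2%. Power, plain/stratified, is 69/68, 63/65, 59/64 and 51/65%.

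**The case against.** The strongest reply is that nothing is broken. The size of the test stays at or below about 5%, the sample size matches the planned test, and at the planned effect the plain test keeps at least its stated 90% power in every setting examined. All of that stands.

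The magnitudes also rest on inputs that the protocol does not supply. With more lopsided strata (assumed 85% >4 cm, 15% node-positive, 90 patients), odds ratios of 2 and 3 give a chi-squared size of 4.6% and 4.4%. Power at 72% vs 45% is then 74.3 vs 75.4% and 74.9 vs 77.3%, and the gain at 81% vs 45% is at most 0.2 points. This stands too, so the size of the loss is a range that includes zero.

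A reader might take the Discussion's admission that heterogeneity could weaken power as direct support. It is not: that remark concerns histology and the various reasons for inoperability, and neither is a stratification factor.

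Finally, the article is condensed, and an analysis plan not shown could add stratification. This is a partial defence. The article does not leave the tests open; it names them, and it mentions adjustment only for quality of life.

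**Conclusion.** The mismatch is in the text, and its direction is clear: conservative tests and some lost efficiency if tumour size and neck nodes are prognostic. Over assumed odds ratios of 1 to 4 per factor, the gain from stratifying the primary test is about 0 to 1 point at 81% vs 45% with 90 patients and 0 to 2 with 72. At 72% vs 45% with 90 patients it is about 0 to 5.5 points. The log-rank loss could be larger, but those figures depend on an assumed median and hazard ratio.

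Stronger readings are tempting but unsupported. A reader might infer that ignoring the strata inflates the false-positive rate or invalidates the primary result; the effect runs the other way. A reader might infer that the trial is underpowered as planned; 72 and 90 reproduce exactly. A reader might also take it as established that the factors are strongly prognostic; the Discussion says only that they serve to balance allocation.

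This is an efficiency and consistency improvement, not a validity error.

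**What to change.** Make the primary test a CMH test stratified by tumour size and neck node status as randomised, and report a stratum-weighted risk difference with its 95% CI. Use stratified log-rank tests for PFS and OS. Keep the unstratified chi-squared and log-rank tests as supportive.

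Pre-specify a rule for pooling sparse strata. At 60%/30% prevalences the smallest cell holds 0.40 × 0.30 × 90 ≈ 11 patients, but at 85%/15% it holds 0.15 × 0.15 × 90 ≈ 2. The rule should depend on stratum counts pooled over arms, not on outcomes by arm.

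The cost is wording in the analysis section or analysis plan, fixed before outcome data are compared by arm. Both factors are already needed for allocation, and the sample size stays at 90.

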**Fig. 2 Fig2:**
[figure not shown]
Observation, assessment, and follow-up schedule

After randomization, eligible participants will receive their treatment planning investigations and are followed-up following the same schedule for both intervention group and control group (Fig. 2) until recurrence, other malignancy or death is confirmed. Treatment duration is approximately 6–7 weeks for IMRT group. All the participants in both groups will be followed up at 2, 4, 6, 9, 12, 15, 18, 21 and 24 months after randomization, with specialized examination, imaging examination, blood routine examination and biochemistry, Karnofsky performance scale, recording of treatment and adverse events assessment done each time. Quality of life (QOL) scale will be assessed at 2, 6, 12, and 24 months. Forward radiation adverse reactions will be evaluated at each follow-up appointment except at 2 months after randomization. In addition, pathological diagnosis and PET/CT examination will be considered by the investigator if imaging examinations are inadequate to assess the primary outcome. Radioactive adverse events were classified by The National Cancer Institute-Common Terminology Criteria for Adverse Events (NCI-CTCAE) 4.0 standard. Chronic radioactive damages were classified by the criteria of Radiation Therapy Oncology Group/European Organization for Research and Treatment of Cancer (RTOG/EORTC), with common signs and severity recorded.

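### Late quality-of-life comparisons would rest on scores carried forward from at or before recurrence, far more often in the IMRT arm than in the I-125 arm

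*Protocol article*

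**What the plan says.** Four statements in the protocol article bear on this point.

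- **Collection** (Initial screening, assessment and follow-up): "Quality of life (QOL) scale will be assessed at 2, 6, 12, and 24 months". Clinic visits are more frequent; patients are "followed up at 2, 4, 6, 9, 12, 15, 18, 21 and 24 months after randomization".
- **End of follow-up** (same section): the schedule applies in both arms "until recurrence, other malignancy or death is confirmed". The text makes no provision for questionnaires after that.
- **Analysis** (Statistical analysis): "A covariance model will be used to compare the QOL between two groups by adjusting the difference of baseline". One paragraph earlier, in the sentence that sets the intent-to-treat basis for the primary analyses, "the last observation carry forward (LOCF) is used for missing values". No other missing-value rule is given.
- **Expected event rates** (Sample size estimation): "local control rate in 1 year was 81 % among subjects with I-125 PBT, and 45 % among subjects with IMRT".

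Under Outcomes, QOL measured by EORTC QLQ-C30 and QLQ-H&N35 is the third of four secondary outcomes. The Discussion lists QOL among the findings meant to show the clinical value of I-125 PBT.

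**The concern.** Each rule could pass on its own. Together they let the expected treatment effect decide whose QOL is measured. A patient whose tumour progresses leaves the schedule, and LOCF then fills the later visits with a score from at or before that progression. Since progression is expected much more often with IMRT, a 24-month comparison would set mostly observed PBT scores against mostly imputed IMRT scores, under a label that suggests both are 24-month values.

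Three consequences follow.

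- The estimated difference mixes the effect of treatment with the time at which follow-up stopped.
- A carried score can run past death, giving a QOL value to a patient who is no longer alive.
- The covariance model treats imputed scores as observed, so its intervals are too narrow.

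Post-recurrence scores that are never collected cannot be recovered at analysis, so the point needs settling while patients are still in follow-up.

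**Working it through.** **The plan's own figure first.** With 0.81 against 0.45, two-sided 5% and 90% power, the pooled-variance formula without continuity correction uses a mean proportion of 0.63:

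n per arm = [1.960 × √(2 × 0.63 × 0.37) + 1.282 × √(0.81 × 0.19 + 0.45 × 0.55)]² / 0.36² = (1.338 + 0.812)² / 0.1296 ≈ 35.7, so 36 per arm and 72 in total. Then 72 / 0.80 = 90, or 45 per arm. The sample size reproduces and is not in dispute. The same two rates are used below.

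**Inputs.** One-year local control S = 0.81 (PBT) and 0.45 (IMRT), from Sample size estimation. The visit and QOL months are from the follow-up section. Recurrence is taken to include progression at the primary site.

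**Assumptions not in the documents.** Where a rate at another month is needed, the local-failure hazard is constant, so the share failed by month m is 1 − S^(m/12). Only local failure is counted. This understates the true share, because under Outcomes "distant metastasis and second primary cancer are not belonged to PD at the primary site", yet other malignancy and death also end the schedule.

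**Two readings of the last score.** Progression is confirmed at a visit, and months 12 and 24 are also QOL visits. If QOL is still taken at the confirming visit, only progression found by the preceding visit (month 9 or 21) leads to a carried score. If it is not, progression up to and including the visit itself counts.

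**Month 12**

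| | PBT | IMRT |
|---|---|---|
| QOL taken at confirming visit: 1 − S^(9/12) | 1 − 0.81^0.75 = 15% | 1 − 0.45^0.75 = 45% |
| Not taken: 1 − S | 19% | 55% |

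**Month 24**

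| | PBT | IMRT |
|---|---|---|
| No local failure after month 12 (lower bound): 1 − S | 19% | 55% |
| Constant hazard, QOL at confirming visit: 1 − S^(21/12) | 31% | 75% |
| Constant hazard, not taken: 1 − S² | 1 − 0.6561 = 34% | 1 − 0.2025 = 80% |

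**Observed IMRT scores at month 24.** 45 × 0.2025 ≈ 9 under constant hazard, and 45 × 0.45 ≈ 20 if nobody fails locally after month 12. The range is roughly 9 to 20 of 45.

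**Adding drop-out.** If the planned 20% drop-out is independent of outcome and has occurred by month 12 (an assumption), the upper IMRT shares become 1 − 0.45 × 0.8 = 64% at month 12 and 1 − 0.2025 × 0.8 = 84% at month 24. For PBT they become 1 − 0.81 × 0.8 = 35% and 1 − 0.6561 × 0.8 = 48%.

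**The case against.** **LOCF is not tied to QOL by name.** Its sentence opens with the primary analyses, and the QOL sentence comes later without mentioning it. Missing-data rules for a secondary outcome may also be left to an analysis plan that is not shown. This stands as a caveat. But LOCF is the only rule stated and is not limited to one endpoint. PFS and OS are handled by Kaplan-Meier, so a repeated score such as QOL is where LOCF most naturally applies. If it does not apply, the covariance model runs on observed cases and compares patients selected for being recurrence-free, which leaves the problem in another form.

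**Follow-up may not stop as strictly as the clause suggests.** The article also says that all participants are followed to 24 months, and OS requires vital status after recurrence. Some later contact is therefore implied. Contact for survival status is not a questionnaire, however, and nothing in the text says that QOL continues.

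**Stronger readings the documents do not support.**

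- A reader might infer that most IMRT patients will have a carried-forward score by month 12. The share is 45% or 55% depending on whether QOL is taken at the visit confirming progression, so a majority is not assured.
- A reader might infer that every carried score precedes recurrence. Some may be taken at the visit where recurrence is confirmed.
- A reader might infer that the 2-month IMRT score falls at the height of acute effects. Visits are timed from randomization, the start of treatment is not dated, and no passage describes such a peak.
- A reader might infer that no baseline QOL is collected because the screening text does not list it. That list is open-ended, the schedule figure is not shown, and the analysis adjusts for baseline, which implies a baseline score.

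**Conclusion.** The point holds as a weakness of the secondary QOL analysis. On the plan's own rates, local failure alone would lead to carried-forward scores in about 15-19% (PBT) against 45-55% (IMRT) at month 12, and about 19-34% against 55-80% at month 24. Month 24 is the firmer case, because more than half of the IMRT scores would be imputed even with no local failure in the second year.

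The missingness is informative and unequal between arms. Its direction cannot be fixed in advance: carrying forward may hide decline after recurrence, mainly in the IMRT arm and so to its advantage, or it may hold early treatment-period scores as late QOL, to its disadvantage. Precision is overstated either way.

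The figures rest on the planning rates being right, on recurrence including progression at the primary site, on a constant hazard for all but the 1 − S figures, and on LOCF applying to QOL. Distant metastasis, other malignancy, death and drop-out would raise the shares. The local-control comparison and its sample size are not affected by this point.

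**What to change.** 1. **Collection (the core of the fix).** State that QLQ-C30 and QLQ-H&N35 continue at the remaining scheduled times (6, 12 and 24 months after randomization) after recurrence, until death. Without this, no analysis can recover post-recurrence QOL.
2. **Model.** For QOL, replace LOCF with a mixed model for repeated measures on all observed scores, with terms for arm, visit, arm-by-visit, baseline score and the two stratification factors (tumour size and neck node metastasis). This model assumes missing at random, so it supplements item 1 and does not replace it.
3. **Death.** Carry no score past death. Report, by arm and visit, the number alive and the number with an observed score, so that readers can see whom each estimate describes.
4. **Sensitivity.** Add one analysis for informative dropout, such as a pattern-mixture or delta-adjusted analysis.

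The cost is a change of wording in the follow-up and analysis sections, some extra questionnaires for patients who have recurred, and modest additional analysis work. The sample size does not change.
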